### Data analysis

#### Healthy change intervention feasibility

Researchers will analyze qualitative data from the focus groups using inductive content analysis [25]. A team approach will be utilized to analyze data with a minimum of three researchers independently reviewing each transcript and identifying emerging themes. The team will then convene to discuss, compare, and merge themes to develop a coding template. NVivo software will be used to assist in data organization.

#### Healthy change intervention effect

The quantitative data will be analyzed in Statistical Package for the Social Sciences (SPSS) version 23. WHO Anthro (version 3.2.2, January 2011) and macros will be used to calculate children’s age- and gender- specific BMI percentile and children will be classified by the World Health Organization | BMI-for-age chart: malnutrition (percentile < 3), low weight (≥3 and < 15), normal weight (≥15 and < 85), OW (≥85 but < 97), and OB (≥97) [31]. The rate at which mothers accurately classify their children’s weight status will be calculated in two ways, i.e., by words or by images. Accurate MPCW by words will be defined as show in Table 2.

**Table 2 Tab2:** Accurate MPCW by words

Children’s actual weight status by BMI percentile	MPCW by words
Malnutrition (< 3 percentile) Low weight (≥ 3 and < 15 percentile)	“underweight” or “a little underweight”
Normal weight (≥ 15 and < 85 percentile),	“Normal weight”
Overweight (≥ 85 but < 97 percentile)	“A little overweight”
Obese (≥ 97)	“Overweight”

With regard to the MPCW by image test, an accurate perception is defined when mothers of underweight and normal weight children select an image smaller than the average image or when mothers of children with OW-OB select the average or a larger image.

McNemar’s Test will be used to test the primary outcome measure, i.e., intervention effect on change in proportion of mother’s accurate recognition of their preschooler’s weight status. The GLM Univariate procedure will be used to determine intervention effects on secondary outcomes e.g., scores of mother’s self-efficacy, feeding practices and children’s BMI percentiles and fat%. The models will include the secondary outcome measures as the dependent variables, treatment condition (intervention versus control) as the fixed factor, and confounding factors (e.g., mother’s education level, children’s gender and age) as covariates. Sub-analyses will be performed to compare intervention effects on both primary and secondary outcomes between the samples from Mexico and Texas, USA.

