#### Outcome evaluation

Baseline and post-intervention data will be collected on all participants. Each mother will receive 25 USD at the end of the intervention for their participation in the data collection. The primary outcome of this study is the proportion of mothers who accurately estimate their children’s weight status. Maternal perception of child’s weight is measured using the Parents’ Perceptions about Their Child’s Appearance and Health Questionnaire [19]. Mothers are asked to indicate their child’s weight status from 5 response options: “underweight”, “a little underweight”, “about the right weight”, “a little overweight”, or “overweight” (MPCW by words). Mothers also checked one of the body sketches (MPCW by image) in the age range 2 to 5 years old [19, 26].

Secondary outcomes include:Change in the maternal feeding styles. Maternal feeding styles is measured using the Caregiver Feeding Style Questionnaire. The questionnaire consists of 19 questions grouped in two dimensions: demandingness and responsiveness. Subsequent calculation of the median of both dimensions places participants in one of the four styles, i.e., authoritative, authoritarian, indulgent, or uninvolved [16].Increased self-efficacy score of maternal influencing on children’s health behavior. Mothers rate their confidence on a 5-point Likert scale ranging from “strongly disagree” to “strongly agree” on these two statements: “I can influence my child’s food choices” and “I can influence my child’s amount physical activity” [27].Improved score of family nutrition and physical activity. The Family and Nutrition and Physical Activity (FNPA) screening tool is used to assess mothers’ practices that may predispose children to becoming overweight [28]. The FNPA tool consists of 20 questions assessing family meals, family eating practice, food and beverage choices, material feeding restriction/ reward practice, child’s screen and activity time, sleep schedule, family activity routine and healthy environment [28]. Each question has four options: i.e., “Never/Almost Never”, “Sometimes”, “Often”, and “Very Often/Always” [28].Reduction or maintenance of the child’s BMI and BFP: The child’s weight is measured by Seca Scale 813 and height by Seca stadiometer 214, the BFP is measured by bioelectrical impedance by InBody 230.

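### As worded, the image rule scores the average sketch as wrong for a normal-weight child and right for an overweight or obese child, which conflicts with Table 2 if that sketch depicts normal weight

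*Protocol article*

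**What the plan says.** All references are to the protocol article.

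- **Outcome evaluation:** "The primary outcome of this study is the proportion of mothers who accurately estimate their children’s weight status". The mother answers in two ways: she picks one of five verbal categories and she marks one of a set of body sketches. The article gives neither the number of sketches nor the weight status that each one shows.
- **Healthy change intervention effect, child's actual status:** BMI-for-age percentile bands, with "normal weight (≥15 and < 85" as the middle band, overweight from the 85th percentile and obese from the 97th.
- **Same section, Table 2 (word rule):** a normal-weight child must be matched with the normal category, an overweight child with the slightly overweight category, and an obese child with the overweight category.
- **Same section, image rule:** perception counts as accurate "when mothers of underweight and normal weight children select an image smaller than the average image". The rule for the two heavier groups is a separate condition, namely that "mothers of children with OW-OB select the average or a larger image".
- **Same section, role of the two versions:** "The rate at which mothers accurately classify their children’s weight status will be calculated in two ways, i.e., by words or by images". McNemar's test is then assigned to the primary outcome without saying which version it uses. The sample size section's assumed change from 50% to 70% does not separate the versions either.

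**The concern.** The trial exists because mothers underestimate. The Background cites underestimation by 68% of mothers of overweight children and 75% of mothers of obese children, and the Discussion makes correcting this misperception the aim. A valid accuracy score should credit a mother who comes to see an obese child as larger than ordinary, and a mother who sees a normal-weight child as ordinary. On the plain meaning of an average image, the image rule does neither.

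At stake is the direction of the measured effect. Some mothers whose perception improves would be counted as unchanged and others as having deteriorated. An intervention that works could therefore look weaker than it is, or look harmful, on this version of the outcome. Because the article leaves open which version is primary, that result could become the trial's main conclusion.

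**Working it through.** The plan states no figure for image accuracy, so there is none to reproduce. The check applies the stated rule to every combination of child status and chosen sketch.

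**Step 1. Rule as written**

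| Child's actual status | Smaller than average | Average | Larger than average |
|---|---|---|---|
| Underweight (below 15th percentile) | accurate | inaccurate | inaccurate |
| Normal weight (15th to below 85th) | accurate | inaccurate | inaccurate |
| Overweight or obese (85th and above) | inaccurate | accurate | accurate |

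This table follows from the text alone.

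**Step 2. The counterpart of Table 2**

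Assumption: the average sketch depicts a normal-weight child. I also read Table 2's normal category as the middle verbal option in the questionnaire.

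| Child's actual status | Smaller than average | Average | Larger than average |
|---|---|---|---|
| Underweight | accurate | inaccurate | inaccurate |
| Normal weight | inaccurate | accurate | inaccurate |
| Overweight or obese | inaccurate | inaccurate | accurate |

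Three of the nine cells differ: normal weight with a smaller sketch, normal weight with the average sketch, and overweight or obese with the average sketch. Two of these credit a sketch that is too small; the third denies credit to the sketch that matches.

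**Step 3. What a before-after test sees**

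| Child | Sketch at baseline → after | Score as written | Contribution to McNemar's test |
|---|---|---|---|
| Obese | average → larger | accurate → accurate | none (concordant) |
| Obese | smaller → average | inaccurate → accurate | improvement |
| Obese | smaller → larger | inaccurate → accurate | improvement |
| Normal weight | smaller → average | accurate → inaccurate | deterioration |
| Normal weight | average → smaller | inaccurate → accurate | improvement |

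Under the Step 2 assumption, the first row loses a real gain and the last two rows have the wrong sign. The second row credits a mother who still sees her obese child as ordinary.

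**Step 4. Illustration of size**

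The article gives neither the sample's weight distribution nor the distribution of sketches chosen, so these are assumptions: no underweight children, every mother picks the average sketch, and a share q of the children is overweight or obese.

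- As written: accuracy = q × 1 + (1 − q) × 0 = q
- Aligned with Table 2: accuracy = q × 0 + (1 − q) × 1 = 1 − q

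| q | As written | Aligned with Table 2 |
|---|---|---|
| 0.2 | 20% | 80% |
| 0.3 | 30% | 70% |
| 0.4 | 40% | 60% |

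On this one response the two rules give opposite scores for every mother. The example is extreme by construction and does not predict the trial's data.

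**The case against.** The strongest reply is that the sketches are not shown and the average one is never tied to a weight status. It may simply be the middle drawing of a series. If that drawing sits at the lower edge of overweight, then scoring everything below it as not overweight, and everything from it upward as overweight or obese, is a coherent two-group cut. Table 2 is also headed as the rule for words, and a coarser rule for a different instrument is not in itself a contradiction. This stands as a limit: the conflict is conditional on what the average sketch depicts. It does not remove the point, because nothing in the article supports the special reading, and the ordinary meaning of average falls in the normal band.

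A reader might infer more than the article supports:

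- **That the rule rewards underestimation in general.** It does not. A mother of an overweight or obese child who picks a sketch below average is still scored inaccurate, and moving up from there earns credit.
- **That most children in the trial are mis-scored.** The normal band spans 85 − 15 = 70 percentile points, but of the reference population. The article gives no weight distribution for this sample and no distribution of choices.
- **That two versions of the outcome inflate the false-positive rate by a known amount.** The article states no significance level and does not say that success on either version is enough. Both answers come from the same mother about the same child, so independence cannot be assumed. What remains is that neither version is named as primary.
- **That the whole primary outcome is unsound.** The word version in Table 2 does not have this defect.

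The sentence may also be a drafting slip that put the average sketch in the wrong group. That would explain the conflict, but the rule would still need correcting before use.

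**Conclusion.** The point holds in a conditional form. It follows from the text alone that the average sketch is scored inaccurate for normal-weight children and accurate for overweight or obese children. That this conflicts with Table 2 rests on one assumption, that the average sketch depicts a normal-weight child. Under it, three of nine scoring cells disagree with the word rule, one intended improvement is invisible to McNemar's test, and another is counted as deterioration.

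The net bias in the trial cannot be calculated from the article; a null or adverse result despite improved perception is possible, not demonstrated. The defect is confined to the image version, but it can reach the primary analysis because the article does not say which version is primary. It is a stated rule that is inverted or unreconciled, not a detail left to a fuller document, and it should be resolved before analysis.

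**What to change.** 1. State what weight status the average sketch represents, and how the other sketches are ordered around it.
2. Reconcile the image rule with Table 2. If the average sketch represents normal weight: underweight is matched by a sketch smaller than average, normal weight by the average sketch, and overweight or obese by a sketch larger than average. If it represents something else, state that anchor and justify the cut-off from it; the key above would then not apply.
3. Name perception by words, scored by Table 2, as the single primary outcome for McNemar's test, with perception by image as secondary.

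The cost is a few sentences in the analysis section and recoding of stored responses, provided that the sketch chosen was recorded and not only the accurate or inaccurate score. No new data collection is needed. The scoring key should be fixed before image results are compared between arms.

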**Methods/Design:**

The “Healthy Change” is a multicenter two-arm randomized trial in four centers. Three centers are in Mexican States (Nuevo Leon, Tamaulipas, and Zacatecas). The fourth center is in San Antonio, Texas, USA. A total of 360 mother-child pairs (90 pairs per center) are to be randomly and evenly allocated to either the intervention or the control group. Intervention group will receive four-session group obesity prevention education. Control group will receive a four-session personal and food hygiene education. The education is delivered by trained peer-mother promotoras. Data will be collected using questionnaires and focus groups. The primary outcome is a change in proportion of mothers with accurate MPCW. Secondary outcomes include change in maternal feeding styles and practices, maternal self-efficacy and actions for managing child excessive weight gain.

McNemar’s Test will be used to test the primary outcome. The GLM Univariate procedure will be used to determine intervention effects on secondary outcomes. The models will include the secondary outcome measures as the dependent variables, treatment condition (intervention/control) as the fixed factor, and confounding factors (e.g., mother’s education, children’s gender and age) as covariates. Sub-analyses will be performed to compare intervention effects on primary and secondary outcomes between the samples from Mexico and Texas, USA. Qualitative data will be analyzed through analysis of inductive content. A combined coding model will be developed and used to code transcripts using the NVivo software.

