## Methods

### Aims

This pilot study aims to develop and test the effects of the “Healthy Change” intervention on changing maternal perception of preschoolers’ weight status among Mexican mothers in México, and Hispanic mothers in San Antonio, Texas. Specific objectives are 1) To test the feasibility of “Healthy Change” intervention when implemented in a childcare setting; 2) To assess the effect of “Healthy Change” intervention on changing maternal perception of their preschoolers’ weight status; and 3) To assess the effect of the “Healthy Change” intervention on changing parenting style, maternal attitude, self-efficacy and practice toward raising healthy weight children.

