### Trial design

The “Healthy Change” study is a multicenter two-arm randomized trial with four research sites, three in Mexico: a) Nuevo León, b) Tamaulipas, and c) Zacatecas, and one in San Antonio, Texas, USA. At each site, two childcare centers are randomly assigned to either the intervention or the attention control group. A total of 360 pairs of preschoolers and their mothers, i.e., 90 pairs per site, are recruited for the trial. Intervention participants will receive a four-weekly group education focusing on maternal perception of children’s bodyweight that facilitate healthy behavioral changes for the family. Control participants will receive a four-session group education on food hygiene and first aids as attention control. The outcomes include change in the proportion of mothers who accurately estimate their children’s weight categories, change in feeding style, maternal self-efficacy and actions taken in managing the child’s excessive weight gain. Data are to be collected at baseline and the end of the four-week group education from both groups. The study began on 08–29-2015, and will end on 11–20-2018.

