### Sample size and statistical power

The primary outcome of this intervention will be the proportion of mothers who adequately estimate their child’s weight status. Assuming the intra-class correlation coefficient (ICC) of 0.03, to detect a change of mother’s accurate estimation of children’s weight status from 50 to 70% with 80% power, 37 mother-child pairs would be required per research center per arm [23]. Accounting for a 15% attrition rate, each research site will enroll 45 pairs of mothers and children for the intervention and another 45 pairs for the control group. The total sample size for this four-center trial will be 360 pairs of mothers and children.

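### McNemar's test, the only test named for the primary outcome, does not compare intervention with control, so the analysis as written cannot show an intervention effect

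*Protocol article*

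**What the plan says.** The Trial design section describes a "multicenter two-arm randomized trial with four research sites". It goes on: "At each site, two childcare centers are randomly assigned to either the intervention or the attention control group". Both arms are measured twice: "Data are to be collected at baseline and the end of the four-week group education from both groups". The control arm receives an attention-control curriculum of similar dose.

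The second objective under Aims is "To assess the effect of “Healthy Change” intervention on changing maternal perception of their preschoolers’ weight status". The abstract defines the endpoint: "The primary outcome is a change in proportion of mothers with accurate MPCW".

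For the analysis, the section on the intervention effect states that "McNemar’s Test will be used to test the primary outcome measure, i.e., intervention effect on change in proportion of mother’s accurate recognition". The abstract repeats this without qualification: "McNemar’s Test will be used to test the primary outcome".

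The same section then gives a general linear model with treatment condition as the fixed factor, but its dependent variables are the secondary outcomes. The planned sub-analyses compare Mexico with Texas, not intervention with control.

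**The concern.** The stated purpose of the primary test (an intervention effect) and the test itself do not match. McNemar's test asks whether a paired proportion moved between two occasions in one set of people. The two arms here are different mothers in different childcare centers, with no individual matching, so the pairing can only be before versus after.

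The text does not say on which mothers the test is run. There are three readings, and none compares the arms:

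- **Intervention arm only.** The randomised control group is discarded.
- **Each arm separately.** Significance in one arm and not in the other is not a test of the difference between arms.
- **Both arms pooled.** The treatment received plays no part.

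In both arms mothers answer the same perception questionnaire twice and children are weighed and measured. Accuracy could therefore change in both arms for reasons unrelated to the curriculum. A before-after test credits such a change to the intervention, which is the error a randomised attention-control arm is there to prevent.

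**Working it through.** **1. Is there a between-arm test for the primary outcome anywhere?**

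| Analysis named | Outcome | Term for treatment arm? |
|---|---|---|
| McNemar's test | Primary | No |
| General linear model | Secondary only | Yes, fixed factor |
| Sub-analyses | Primary and secondary | Compares countries; presupposes an intervention effect but gives no way to estimate it for the primary outcome |

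No sentence supplies a between-arm test or effect estimate for the primary outcome.

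**2. What was the trial sized for?** The Sample size section plans "to detect a change of mother’s accurate estimation of children’s weight status from 50 to 70% with 80% power", with an ICC of 0.03, and arrives at 37 pairs per research center per arm. Alpha and sidedness are not stated. Treat this as two independent proportions with unpooled variance and four clusters per arm:

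- n per arm without clustering = (z_α + z_β)² [p1(1−p1) + p2(1−p2)] / (p1−p2)². At one-sided 5%: (1.645 + 0.842)² × (0.25 + 0.21) / 0.04 = 71.1.
- With m pairs in each of four clusters, 4m = n[1 + (m−1) × 0.03], so m = 0.97n / (4 − 0.03n) = 36.9, i.e. 37. This matches the stated figure.
- At two-sided 5%, n = 90.3 and m = 67.8, which does not match.
- Attrition: 37/0.85 = 43.5, i.e. 44, against 45 enrolled. 45 × 2 × 4 = 360, as stated.

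The stated 37 is thus consistent with a between-arm comparison of clusters. Two formulas that ignore the ICC also give about 37: a one-sample one-sided test (36.5), and two-sided McNemar with no mother moving from accurate to inaccurate (36.8). The match is therefore supporting evidence, not proof.

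**3. How often would McNemar's test be significant with no intervention effect?** Inputs: 37 × 4 = 148 completers in the intervention arm, exact two-sided test at 5%, clustering ignored. Assumed: a rise d in accuracy common to both arms, and a proportion D of mothers whose two answers differ in accuracy. Then the probability of moving to accurate is (D + d)/2 and of moving to inaccurate (D − d)/2. Probability of a significant result:

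| Shared rise d | D = 20% | D = 30% | D = 40% | D = 50% |
|---|---|---|---|---|
| 0 points | 0.03 | 0.04 | 0.04 | 0.04 |
| 2 points | 0.06 | 0.05 | 0.05 | 0.05 |
| 5 points | 0.21 | 0.16 | 0.13 | 0.11 |
| 10 points | 0.74 | 0.56 | 0.44 | 0.36 |

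A second calculation used the normal approximation, a 50% baseline and a within-mother correlation of 0 to 0.5. It gives 14% to 23% for 5 points and 41% to 68% for 10 points.

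Pooling both arms (n = 296) makes it worse: at 10 points the exact rate is 0.76 to 0.97 for D from 40% down to 20%.

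**4. What power does the between-arm comparison have?** With 37 analysed per cluster, the design effect is 1 + 36 × 0.03 = 2.08 and the effective size is 148/2.08 = 71 per arm. For 50% versus 70%, before any gain from adjusting for baseline:

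- one-sided 5%, normal: about 80%
- two-sided 5%, normal: about 69%
- two-sided 5%, t on 6 df (4 versus 4 centers): about 55%
- two-sided 5%, t on 3 df (centers compared within site): about 40%, if accounting for site removes no variance

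**The case against.** The strongest points on the other side are these.

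- **The data can answer the question.** Both arms are measured at both times, so a valid between-arm analysis is possible. This stands: the fault lies in the analysis as written, not in the design.
- **The within-arm reading is inferred.** The text does not say in which mothers the test is run, and the country sub-analyses show that the authors have an intervention effect on the primary outcome in mind. An unseen analysis plan might add detail. But the article commits to a named test, and that test has no arm term under any of the three readings.
- **Shared drift is assumed.** The documents give no figure for change in the control arm, do not say that mothers are told their child's measurements, and describe a control curriculum on hygiene and safety rather than weight. This stands as a limit on the size: with a shared rise of 0 to 2 points, the rejection rate stays at about 3% to 6%. It does not touch the logic, because a test without a control comparison offers no way of knowing which row of the table applies.
- **This is a pilot, with feasibility as its first objective.** That softens the consequence but does not excuse the test: the second objective is an effect, and the sample size is powered for it.

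**Conclusion.** The concern holds and must be fixed. The article names McNemar's test for the intervention effect on the primary outcome; the test cannot estimate that effect, and nothing else in the document does. The control arm and the randomisation contribute nothing valid to the primary conclusion as planned.

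The size is illustrative. With no true effect and 148 completers, a shared 10-point rise gives a significant intervention-arm result in 44% to 74% of trials, and a 5-point rise in 13% to 21%, for 40% down to 20% discordance. At 50% discordance the rates fall to 36% and 11%. These figures rest on the assumed drift and discordance and ignore clustering, as the test itself does despite the ICC in the sample size. The finding that no between-arm test exists rests on no assumption.

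**What to change.** In the section on the intervention effect and in the abstract, replace McNemar's test as the primary analysis with a between-arm comparison:

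- Outcome: accurate perception (yes/no) after the intervention. Model it on treatment arm, adjusted for baseline accuracy and site, with the childcare center as the cluster.
- Use a method that is valid for few clusters. One workable form has two stages: regress post-intervention accuracy on baseline accuracy and site without arm, average the residuals within each center, and compare the center means between arms with a t-test. With two centers per site this is 4 versus 4; the degrees of freedom should allow for site and for any third center added under the recruitment rule. A mixed logistic model or GEE with small-sample correction is an alternative.
- Report the adjusted difference in proportions with its 95% CI.
- Keep McNemar's test, if wanted, only as a within-arm description.

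The cost is a change of wording; no new data are needed. The sponsor should also state alpha and sidedness and restate power for this comparison. At two-sided 5% (an assumption) it is about 69% by the normal approximation, and 40% to 55% with a t reference on 3 to 6 df, rather than 80%.

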### Childcare center recruitment and randomization

Each research site will recruit a total of 90 pairs of preschoolers and their mothers with 45 pairs in the intervention and 45 pairs in the control group. Each research site initially recruits two childcare institutions with similar size and demographic profiles to participate in the study. The administrators of these centers are informed of the possibility of being assigned to either the intervention or the control group. Prior to participant recruitment, the two or three childcare institutions at each research center are randomly assigned to one of the two treatment groups using a random number table. In the event that an insufficient sample is recruited from the participating centers, a third center will be added to ensure adequate sample in the designated group.

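### Childcare centres are randomised and the sample size assumes clustering, but the stated analyses have no centre term; a between-arm test at nominal 5% would run at about 17%

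*Protocol article*

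**What the plan says.** **Unit of randomisation.** Under Trial design: "At each site, two childcare centers are randomly assigned to either the intervention or the attention control group". With four sites this gives eight centres, four per arm. Under Childcare center recruitment and randomization: "the two or three childcare institutions at each research center are randomly assigned to one of the two treatment groups". The same section puts this step before mothers are recruited and provides that, if recruitment falls short, "a third center will be added to ensure adequate sample in the designated group". Eight centres is therefore the default, not a fixed number.

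**Abstract.** Its Methods/Design paragraph says of the 360 mother-child pairs that they "are to be randomly and evenly allocated to either the intervention or the control group".

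**Sample size.** The calculation begins "Assuming the intra-class correlation coefficient (ICC) of 0.03". It arrives at 37 pairs per site per arm for 50% versus 70% with 80% power, raised to 45 for 15% attrition.

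**Analysis.** Under Healthy change intervention effect, the primary outcome is tested with McNemar's test. For the others, "The GLM Univariate procedure will be used to determine intervention effects on secondary outcomes"; the model has arm as the fixed factor and covariates such as the mother's education and the child's sex and age. The section adds: "Sub-analyses will be performed to compare intervention effects on both primary and secondary outcomes between the samples from Mexico and Texas, USA". No random effect, generalised estimating equation, robust variance, centre-level summary, or site or centre term is mentioned anywhere.

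**The concern.** Mothers in one centre share a setting, a peer educator and the group sessions, so their outcomes are correlated. When whole centres are allocated, that correlation goes straight into the variance of the arm comparison. A model that treats about 296 mothers (8 × 37) as independent uses 294 residual degrees of freedom; the design supplies 8 − 2 = 6, or 4 − 1 = 3 if centres are analysed as site pairs. Standard errors come out too small and false positives too frequent. The article assumes clustering when it sizes the trial and omits it when it analyses the data.

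The between-country comparison is the most fragile. By default Texas has one centre per arm, so its treatment effect cannot be told apart from the difference between two centres. The article intends the results to support funding for a large trial, so a spurious effect would have consequences.

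**Working it through.** **Inputs from the article:** ICC 0.03; 50% versus 70%; 80% power; m = 37 evaluable pairs per centre (45 enrolled); four centres per arm by default. **Assumed:** two-sided 5% level (neither level nor sidedness is stated), and the ICC, given once for maternal accuracy, applied to whichever outcome is tested.

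**1. The article's own 37.** With one-sided 5%, unpooled variance and four clusters per arm:
- Independent n per arm = (1.645 + 0.842)² × (0.25 + 0.21) / 0.20² = 71.1.
- Solve 4m = 71.1 × [1 + (m − 1) × 0.03]: m = 71.1 × 0.97 / (4 − 71.1 × 0.03) = 36.9, so 37.
- 37 / 0.85 gives 44 (45 stated); 4 × 2 × 45 = 360.

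This route reproduces 37, but it is not the only one: a two-sided McNemar calculation with 20% discordant pairs and no clustering gives 36.8. With a two-sided level and the same clustering, m would be about 68 (unpooled) to 75 (pooled).

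**2. Type I error of a between-arm test that ignores centre.**
- Design effect = 1 + 36 × 0.03 = 2.08; √2.08 = 1.442.
- True level = 2 × [1 − Φ(1.96 / 1.442)] = 17.4%.
- At m = 45: design effect 2.32, true level 19.8%.

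| Assumed ICC (m = 37) | Design effect | True level of nominal 5% test |
|---|---|---|
| 0.01 | 1.36 | 9.3% |
| 0.02 | 1.72 | 13.5% |
| 0.03 | 2.08 | 17.4% |
| 0.05 | 2.80 | 24.1% |

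A simulation of 40,000 null trials at ICC 0.03 gave 17.1% for ordinary least squares, 18.4% for a chi-square test and 5.1% for a t-test on centre means with 6 df.

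**3. Interval width.** Both the standard error and the quantile change:
- 6 df: 1.442 × 2.447 / 1.96 = 1.80 times the naive width.
- 3 df (site pairs): 1.442 × 3.182 / 1.96 = 2.34 times.

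**4. Power for 50% versus 70%.**
- Effective n per arm = 148 / 2.08 = 71.2; SE = √(0.46 / 71.2) = 0.0804; 0.20 / 0.0804 = 2.487.
- One-sided normal test: Φ(2.487 − 1.645) = 80%, matching the article.
- Two-sided normal test: Φ(2.487 − 1.96) = 70%.
- Two-sided t-test (non-central t): 55% on 6 df (54.5% simulated), and 40% on 3 df with the same SE.
- At m = 45 with no attrition, 6 df gives 59%.

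**5. Mexico versus Texas.** By default there are three centre pairs in Mexico and one in Texas. The single Texas pair gives no estimate of its own between-centre variance. An error term exists only if the Mexican variance is assumed to hold in Texas, and three pairs supply 3 − 1 = 2 df.

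**The case against.** **Details may sit in an unseen analysis plan.** Silence would be no finding. But the article names the procedures and lists the model terms. The covariate list is open-ended, yet its examples are all individual-level. Adding site there would not capture differences between centres within a site, and centre as a fixed effect would absorb the arm contrast, because each centre belongs to one arm.

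**The 17% does not describe the primary analysis.** This stands. A reader might infer that the primary test runs at 17%; the documents do not support that. McNemar's test is a paired before-after test in which stable centre differences cancel. It also ignores clustering, but any inflation depends on how change clusters, and no such figure is given. That it does not compare the arms is a separate defect.

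**The ICC may not transfer.** This stands too. Covariates could lower it. If part of the 0.03 reflects differences between sites, those largely balance out, because each site contributes to both arms. The table shows how the result moves.

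**The abstract is only loosely worded.** A reader might infer that pairs really were individually randomised. The Trial design and recruitment sections rule that out, so this is a wording correction.

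**Mexico versus Texas.** A reader might infer that no valid error term can exist. That goes too far: borrowing the Mexican variance gives about 2 df, which is very weak but not undefined. Also, one centre per arm in Texas is only the default. A single added centre would still leave one arm there with one centre.

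**It is a pilot.** Feasibility is the first objective, but the other two assess effects, so the pilot label softens the point without removing it.

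**Conclusion.** The point holds. The stated analyses leave out the unit that was randomised, although the sample size allowed for it. For the between-arm GLM analyses, under the two assumptions above, the false-positive rate is roughly three times nominal, and still nearly double at a third of the planned ICC. The article does not mention confidence intervals, but any computed from the same models would be too narrow by the factors in step 3. The degrees of freedom rest on the default eight centres. For McNemar's test the direction of the fault is clear, but its size cannot be given from the documents.

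The drop in power from 80% to about 55% should not be put down to clustering alone, since the sample size already carried the ICC. On the reconstruction that reproduces 37, about 10 points come from moving to a two-sided level and about 15 from having only 6 degrees of freedom.

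**What to change.** - Describe the trial as cluster-randomised by childcare centre within site, and correct the allocation sentence in the abstract.
- Compare arms on every outcome, including the primary, with the childcare centre as cluster. Use centre-level summaries with a t-test (6 df, or 3 df if site pairing is kept), or a mixed model with a random centre intercept and small-sample degrees of freedom. State which, and how a third centre at a site enters the analysis.
- State the significance level and sidedness, and restate power on that basis: about 55% for 50% versus 70% on 6 df, two-sided.
- Report the Mexico and Texas results descriptively, without a significance claim, and say why.

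This changes analysis and wording only; no new data are needed. The cost is wider intervals and a less favourable stated power.
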